## Abstract

**Background:**

Chronic primary low back pain (CPLBP) is highly prevalent and associated with physical impairment and psychological distress. Fear avoidance (FA) is one contributing factor in the development and persistence of CPLBP. Previous studies proved existing connections between pain, physical activity, stress, and FA, which is also present in pain-free individuals. However, the roles of FA and psychophysiological stress responses have not been systematically disentangled and related to movement patterns combined in one standardized experiment involving pain induction.

**Methods:**

To address this gap, 76 pain-free participants (20: phase 1; 56: phase 2) will perform standardized movement tasks (Back Performance Scale, Sit-To-Stand-Test) with and without wearing a back pain simulator in a within-subject design. Movement will be recorded with wearable sensor-based and novel radar-based motion capture technology. Additionally, psychophysiological stress parameters (e.g., salivary cortisol, heart rate variability), and self-reports on stress, pain, and FA will be assessed. This will be followed by a qualitative feasibility and acceptability interview in phase 1. In this phase, we will evaluate the feasibility and acceptability of a novel back pain simulator enabling a standardized simulation of low back pain, and the motion capture technology. Phase 2 will investigate the effects of pain induction on self-reported pain, back pain-related movement parameters, and stress responses. Associations of these factors with FA will be analyzed. We anticipate high feasibility and acceptability. We expect higher pain ratings, lower mobility, and higher stress responses in the pain condition compared to the control condition. We expect FA to moderate mobility and stress responses in the pain condition.

**Discussion:**

This study protocol establishes an experimental paradigm to investigate the association of pain, FA, movement, and stress in healthy samples under controlled pain conditions. This paradigm aims to contribute to a deeper understanding of the interplay of psychological and physiological mechanisms in CPLBP.

**Trial registration:**

OSF, osf-registrations-rt2ca-v1. Registered April 2, 2025, https://doi.org/10.17605/OSF.IO/RT2CA; osf-registrations-vsmce-v1. Registered September 18, 2025, https://doi.org/10.17605/OSF.IO/VSMCE.

## Introduction

Chronic low back pain (CLBP) is a common health condition. Prevalences range from 3.9% and 25.4%, depending on factors such as age, sex, or the pain definition used [1]. According to the International Classification of Diseases (ICD-11), low back pain (LBP) is pain located between the inferior gluteal folds and the costal margin [2]. Pain that lasts longer than 3 months is considered chronic pain [3]. Two different types of chronic pain are distinguished in the ICD-11 [4]: chronic primary pain and chronic secondary pain. Chronic primary pain is characterized by significant distress and disability and not better accounted for by a specific secondary form of chronic pain. Regarding chronic low back pain, chronic secondary low back pain refers to consequences of a specific pathology (e.g., tumor, herniated intervertebral disc) or surgery [5]. Chronic primary low back pain (CPLBP) comprises all forms of chronic low back pain accompanied by distress or disability and not better accounted for by a chronic secondary pain; previously these were often – in felicitously – referred to as “non-specific”.

Biological, psychological, and social factors contribute to the development and persistence of CPLBP [6–8]. A central psychological factor in many CPLBP patients is the tendency to avoid physical activities due to the belief that such activities may worsen pain or cause (re-)injury [9]. This behavior, known as fear avoidance (FA; [10,11]) often relates to specific movements associated with back pain, such as lifting objects or bending down. FA is observed in up to 40% of CPLBP patients [12]. According to the original FA model, movement avoidance arises through classical conditioning: The affected person associates pain with specific physical activities, which are then perceived as threatening and potentially harmful as they might cause pain or further injury [9,13,14]. Neurobiological investigations failed to identify neural correlates of the hypothesized fear response [15,16], hypothesizing that beliefs and expectations are more relevant than a conditioned fear response. This is also supported by studies reporting FA beliefs in healthy, pain-free persons [17,18], who may have acquired them via semantic learning, e.g., due to the proliferation on back-related advice [19,20].

Irrespective of how FA beliefs arise, they can have wide-ranging consequences across physical, psychological, social, and societal domains [21]. On a physical level, continued inactivity may lead to deconditioning, increased pain sensitivity, and further functional decline, potentially resulting in a vicious cycle of disability [22,23]. Psychologically, FA is associated with feelings of helplessness [24], depressive symptoms [11,23], and general mental distress [23]. It has also been linked to poorer psychological and functional treatment outcomes in chronic pain patients [23]. Socially, FA can lead to disengagement from both professional and private life [21], leading to a reduced quality of life. These effects translate into both direct costs due to higher healthcare utilization and prolonged treatment and indirect costs, such as increased sick leave and work loss [25].

If avoidance of a movement is not possible, many CPLBP patients with FA exhibit guarded movements, such as stiffening to protect the spine [26,27]. These protective movements have been examined using surface electromyography (sEMGt), sensor-based motion capture systems, and psychometric assessments.

SEMGt studies have analyzed trunk muscle activity during gait tasks, with mixed results in relation to FA behavior [28,29]. Ghamkhar and Kahlee [29] reported increased activity in muscles associated with back pain, whereas Pakzad et al. [30] found no significant change in overall muscle activation levels, but observed altered variability in muscle activation patterns. Some studies employed sensor-based motion capture systems to assess FA-related movement patterns during potentially threatening movement tasks, both in persons with CPLBP [27] and pain-free individuals [26]. Matheve et al. [27] identified a reduced lumbar range of motion while Knechtle et al. [26] observed decreased lumbar flexion during tasks rated as potentially harmful. Most of these studies focus only on certain muscle groups, a single movement or mobility parameter, resulting in a lack of a standardized, integrated paradigm.

Together with fear-related behavioral patterns, stress responses are a relevant factor in CPLBP (e.g., [23]). Stress in this context refers to both physiological responses (i.e., activation of the hypothalamic-pituitary-adrenal (HPA) axis and the autonomic nervous system (ANS)) and psychological reactions to actual or anticipated threats. Stress can be triggered by pain itself, by movements, or by the expectation of pain. Patients with CPLBP often report elevated stress levels during or after physical activity [31] as well as anticipatory distress before movements perceived as harmful [32]. Like pain, stress is modulated by psychosocial factors such as fears, beliefs, and cognitive appraisals [33–36]. This suggests that individual differences in coping and interpretation of pain-related stimuli may influence stress responses, potentially interacting with FA mechanisms. Although altered stress regulation has been hypothesized in CPLBP, empirical evidence remains inconsistent [37], pointing to substantial heterogeneity in psychological and physiological stress responses. This emphasizes the importance of accounting for potential sources of variation in the interaction between stress and pain.

To integrate current findings and guide further research, Timmers et al. [37] proposed a threat learning model, including FA beliefs as a mediator between stress responses and chronic pain. Findings partially support and partially contradict this model [32,38]. The complexity of both acute stress responses (e.g., [35,39]) and chronic pain mechanisms [40] further complicates the understanding of their interaction [37]. As both stress and pain are complex and constantly interacting, research in FA, especially in relation with stress responses, can be challenging. We will approach these challenges with a standardized and integrated experimental paradigm considering different measurements for both FA and stress responses.

Our novel integrated paradigm will enable research on the interactions between FA, pain, actual movement patterns, and biopsychological stress responses, which has not been previously undertaken. Comprehensive research on FA faces methodological challenges, particularly with the integration of multimodal data, such as self-report data, movement information, and biopsychological stress markers. Most studies rely on self-report measures or imagery tasks, as actual movement tasks are burdensome, potentially painful for patients, and require complex equipment (e.g., [41]).

Advancements in sensor technology now allow simultaneous measurement of multiple parameters (e.g., movement kinematics, muscle activity), enabling more integrated assessments. Investigating FA in pain-free individuals offers additional insight, as guarded movements also occur in this group [26], though with notable differences. In contrast to pain-free individuals, patients show higher FA, lower functional capacity, and greater overgeneralization of fear [42,43]. Thus, data from actual movement behavior in pain conditions remain essential for understanding FA processes [27].

In summary, there is a lack of an experimental paradigm to investigate the association of pain, FA, movement, and stress under controlled pain conditions with focus on the integration of multimodal data. With the study described in this study protocol, we want to address this gap.

This study protocol comprises a study that is part of a subproject within the interdisciplinary Collaborative Research Center “Empatho-Kinaesthetic Sensor Technology (EmpkinS)”. The goal of EmpkinS is to research minimally invasive, patient-centered diagnostic approaches in medicine and psychology. Phase 1 serves as a proof of concept for both the measurement technologies and experimental procedures, paving the way for phase 2 and following studies. Phase 1 has two aims: (1) assessing the feasibility and acceptability of a back pain simulator to induce temporary lower back pain and (2) testing the feasibility and acceptability of the study setup, i.e., the pain-related movement tasks in combination with the employed sensor technology. The acceptability and feasibility of the back pain simulator and the study setup will be evaluated exploratory in a qualitative interview.

Phase 2 will examine differences between participants with and without experimentally induced lower back pain in back-pain-related movement parameters during standardized movement tasks and investigate the related stress responses. In addition, we will collect self-report data on FA and investigate whether FA moderates the movement parameters and stress responses in the pain condition.

The following hypotheses will be tested:

(1) The task-related ratings of pain intensity are higher in the condition with the back pain simulator (PainSim+) than without (PainSim-).(2) The fear of movement ratings are higher in the condition with the low back pain simulator (PainSim+) than without (PainSim-).(3a) The task-related ratings of motion impairment are higher in the condition with the back pain simulator (PainSim+) than without (PainSim-).(3b) The mobility (measured through lumbar range of motion (LROM), lumbar flexion (LF), and movement velocity (MV)) is lower in the condition with the low back pain simulator (PainSim+) than without (PainSim-).(3c) Observer ratings of performance of task execution are worse in the condition with the low back pain simulator (PainSim+) than without (PainSim-).(4a) The task-related ratings of emotional distress are higher in the condition with the low back pain simulator (PainSim+) than without (PainSim-).(4b) The subjective stress ratings is higher in the condition with the low back pain simulator (PainSim+) than without (PainSim-).(4c) The heart rate variability (HRV) is lower in the condition with the low back pain simulator (PainSim+) than without (PainSim-).

In exploratory analyses, we will examine whether even in this analogue sample self-reported FA is associated negatively with mobility and HRV, and positively with subjective stress reports, salivary stress markers (alpha-amylase, cortisol), and pain ratings.

This integrated design allows for the combined assessment of physiological stress responses, behavioral changes, and movement-related aspects across standardized back-stressing movements.

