### Statistical methods

Qualitative analysis on feasibility and acceptability in phase 1 will be carried out with MAXQDA Analytics Pro [80]. Data of phase 2 will be analyzed using a repeated-measures design. Correlations of dependent variables will determine if multivariate analyses of variance (MANOVAs) or separate analyses of variance (ANOVAs) are indicated, following common recommendations of moderate intercorrelation [81].

The first MANOVA will include the within-subjects factor *condition* (PainSim + vs. PainSim-) and dependent variables measuring task-related fear of movement, pain intensity, impairment and emotional distress. A second MANOVA will assess *mobility* (LROM, LF, MV). And a third MANOVA will examine stress (HRV, salivary cortisol, salivary amylase, subjective stress) in the same manner. Psychophysiological data (e.g., HRV-data) that deviate (significantly) from the other data (i.e., outliers) will be excluded in accordance with the established practices in the literature. The pattern of missing data is tested with MCAR-test. If the missing data is missing completely at random, we will conduct multiple imputation.

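### Phase 2 states an aim of moderation by fear avoidance, but the only FA analysis described is an association, which does not test moderation

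*Protocol article*

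**What the plan says.** The aim appears twice as moderation. The Introduction says phase 2 will "investigate whether FA moderates the movement parameters and stress responses in the pain condition". The Methods part of the abstract turns this into a prediction: "We expect FA to moderate mobility and stress responses in the pain condition".

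The analysis is described as association. The exploratory paragraph at the end of the Introduction will examine whether "self-reported FA is associated negatively with mobility and HRV, and positively with subjective stress reports", and adds salivary markers and pain ratings to the list. The abstract says "Associations of these factors with FA will be analyzed". None of hypotheses 1 to 4c involves FA; each is a contrast of PainSim+ with PainSim-.

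Under Statistical methods, the sentence that begins "The first MANOVA will include the within-subjects factor" names condition and no other factor. The mobility measures go into a further model, for which no additional factor is mentioned. The stress outcomes are handled likewise: "third MANOVA will examine stress (HRV, salivary cortisol, salivary amylase, subjective stress) in the same manner". No FA term, condition x FA term or regression of a difference score is given. The Explorative analyses and Fear avoidance sections define the FA measure (TSK-G total score, taken at baseline) but no model.

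**The concern.** In a within-subject design with two conditions, FA moderates the response to pain if the PainSim+ minus PainSim- difference varies with FA. A correlation of FA with mobility or stress is a different quantity. A participant with high FA may move stiffly both with and without the simulator, which gives an association and no moderation. The Introduction makes this plausible, since it reports FA beliefs and guarded movement in pain-free people.

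If the text is followed as it stands, no described analysis tests the stated aim. An FA association of equal size in both conditions could not be told apart from moderation. If FA acts in opposite directions in the two conditions, an association pooled over conditions would tend to miss it.

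**Working it through.** **The plan's own figure.** Sample size calculation gives d = 0.40, alpha = 0.05 and power 0.80, leading to N = 51. A paired t-test with d = 0.40, two-sided 5% (sidedness is not stated), has power 0.7999 at N = 51 and 0.808 at N = 52, so 51 reproduces within rounding. Adding 10% gives 51 x 1.10 = 56.1, stated as 56. This calculation concerns the condition contrast and says nothing about FA.

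**What each analysis estimates.** Write the outcome as Y1 = a1 + b1 x FA + e1 in PainSim+ and Y0 = a0 + b0 x FA + e0 in PainSim-.

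- Association within PainSim+: slope b1.
- Association with the mean of both conditions: slope (b1 + b0)/2.
- Condition x FA interaction, equivalently the difference Y1 - Y0 regressed on FA: slope b1 - b0.

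Moderation is b1 ≠ b0. Only the third analysis targets it.

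**Size, by simulation.** N = 51, two-sided 5%, 20,000 replicates, FA and outcomes with unit variance. The documents give no slopes or correlations. The slopes below are assumptions, and so is the residual correlation between conditions, set at 0.5 and 0.8. Cells are percentages of trials with a significant result.

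| b1 / b0 | Association, PainSim+ | Association, condition mean | Condition x FA |
|---|---|---|---|
| -0.30 / -0.30 (no moderation) | 58 | 63-70 | 5 |
| -0.30 / 0 (moderation) | 58-59 | 20-23 | 56-90 |
| -0.15 / +0.15 (moderation) | 18-19 | 5 | 56-90 |

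The PainSim+ association gives practically the same rate in the first two rows, so it cannot separate no moderation from moderation. A separate run of 4,000 replicates with a correlation of 0.4 in both conditions (again no moderation) gave 85% for PainSim+, 94% for the mean and 4.8% for the interaction.

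**Check on the first row by formula.** Power for a correlation r is approximately Φ(atanh(r) x √(N - 3) - 1.960).

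- PainSim+: r = 0.30, so 0.3095 x √48 - 1.960 = 0.184, power 57%.
- Condition mean: residual variance is 0.91 x (1 + ρ)/2, which is 0.6825 at ρ = 0.5 and 0.819 at ρ = 0.8. Then r = 0.30/√(0.09 + 0.6825) = 0.341 or 0.30/√(0.09 + 0.819) = 0.315, power 69% or 62%.

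Both agree with the simulation.

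**What the interaction can detect.** The same formula is applied to r, the correlation of FA with the difference score.

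- Smallest r with 80% power: tanh((1.960 + 0.842)/√(N - 3)) = 0.38 at N = 51 and 0.37 at N = 56.
- Power at N = 51 / 56: 29% / 31% for r = 0.2; 57% / 62% for r = 0.3; 84% / 87% for r = 0.4.
- N for 80% power: 194 for r = 0.2, 85 for r = 0.3, 47 for r = 0.4.

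**Which outcomes have a value per condition.** LROM, LF, MV and HRV are recorded during both sets of tasks, and the SSSQ-G is given before and after each set. For saliva the article conflicts with itself. Lab appointment places s2 after the first set and s3 after the second. Stress (phase 2) places s2 after both sets and s3 15 minutes later. On the second schedule cortisol and amylase have no separate value per condition, so no difference score exists.

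**The case against.** The FA question is exploratory, and a condensed article commonly leaves exploratory model terms to a fuller plan; two OSF registrations are cited and not shown. That stands as far as it goes: the absence of an FA term under Statistical methods does not prove that none is planned. It does not remove the mismatch, because the article itself names the FA analysis, and what it names answers a different question from the stated aim.

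The PainSim+ association is also the reading closest to the phrase about the pain condition, and when FA matters only under pain it detects the effect in about 58% of trials, no worse than the interaction at the lower assumed correlation (56%). This is true, so it would be wrong to say that real moderation is generally missed. The difficulty is that the same test is significant equally often when there is no moderation.

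A reader might infer several stronger things that the documents do not support:

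- That the study cannot answer the question. The limit lies in the analyses as written, not in the design.
- That the planned association is a pooled main effect of FA. The article does not say whether it is pooled or within PainSim+.
- That an association will be reported as moderation. No section says so.
- That the paradigm's main claim rests on this analysis. All numbered hypotheses are condition contrasts, and the Discussion describes the aim as investigating association.

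**Conclusion.** The point holds in this form: moderation by FA is a stated aim and expectation of phase 2, and none of the analyses described tests it. That association is not evidence of moderation follows from the definitions and needs no assumed values. The percentages do rest on assumed slopes and correlations and serve as illustration: with equal slopes of -0.30, an association is found in about 58 to 70% of trials and the interaction in 5%. The hypotheses on condition and the sample size are unaffected. Either the analysis or the wording of the aim should change, preferably before phase 2 data are analysed, so that the choice is not made after seeing results.

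**What to change.** In the exploratory paragraph of the Introduction and in Statistical methods, state the FA analysis as the interaction of condition with mean-centred, continuous TSK-G in the repeated-measures model. Equivalently, regress the PainSim+ minus PainSim- difference on TSK-G. Include condition order in the model. Apply it to outcomes with a separate value per condition: LROM, LF, MV, HRV and SSSQ-G. Include cortisol and amylase only once the saliva timings in Lab appointment and Stress (phase 2) have been reconciled so that each condition has its own value. Keep the word moderation for this interaction and report slopes within each condition as descriptive.

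Label the analysis exploratory, since power is adequate only for correlations of about 0.37 to 0.38 or more and several outcomes are tested.

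If the interaction is not wanted, replace the moderation wording in the abstract and the Introduction with association.

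The cost is one model term on data already collected, or an edit to two sentences. The downside is modest precision and a few more exploratory tests.

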## Materials and Methods

### Ethics approval and consent to participate

The study was approved by the Ethics Committee of the Medical Faculty of the Friedrich-Alexander-Universität Erlangen-Nürnberg (ethical approval codes for studies: 25–21-S) and will be conducted in accordance with the Declaration of Helsinki.

All participants will give written informed consent before testing. Prospective participants will be provided with information about the study and data protection when opening the screening-link. Additionally, the informed consent document will be available for the participants as a PDF via a download link prior to participation. If questions arise, participants can contact the study team at any time of study conduction via an email address noted on flyers, posters, etc. The informed consent consists of several parts: consent to participating in the study in general, use of salivary samples, data protection, video and audio recordings, and handling of incidental findings. This enables participants to agree to certain parts of the study procedures while not agreeing to others (e.g., salivary samples can only be used within the concerning study but not in studies with similar research questions).

